The first 1,000 days of life are a vital period that play a crucial role in the development of the immune, endocrine, metabolic, motor, and other developmental pathways. Maternal nutrition and lifestyle choices in preconception and during pregnancy have significant influences on the health, growth, and development of the fetus. Research shows that a maternal diet low in protein is connected to changes in the structure of the liver of the fetus and low birth weight (14), while a diet rich in fat effects adipocyte metabolism, fetal growth, and fat mass in the offspring (15, 16). Maternal anemia and iron, folate, or vitamin B12 deficiency during pregnancy is associated with an increased risk of fetal growth restriction, premature birth, and low birth weight (17–19). The effect of maternal nutrition on the cognitive capability and neurodevelopment of offspring is well established, particularly in the context of micronutrient deficiencies. Vitamin B12 deficiency is associated with spina bifida and infant insulin resistance (20), and maternal iodine deficiency with hypothyroidism. Prenatal maternal iron deficiency is associated with decreased myelination, disturbance in monoamine neurotransmitter synthesis and hippocampal energy metabolism in offspring (21), and there is evidence of an association between increased consumption of essential long-chain omega -3 fatty acids during pregnancy and better infant performance in development assessments, verifying the link between prenatal and postnatal diet to specific aspects of the brain development (22). The effect of prenatal maternal nutrition on neurodevelopment outcomes in children is not exerted solely through the effect of maternal nutrition on fetal growth and birth outcomes. It persists into the postnatal period, by impacting the quality and quantity of breast milk, maternal mood, and infant feeding practices.

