### Statistical Analysis and Sample Size Calculation

The data collected will be checked for accuracy and completeness and will be entered into the Statistical Package for Social Science (SPSS) software, using the most current version. The primary aim of the study is to examine the associations between maternal nutrition (e.g., weight gain, micronutrient status, etc.) and infant health outcomes (e.g., growth rate, dietary diversity score, feeding practice score, etc.). Given the somewhat limited data on the above-mentioned relationships, for power calculation an *r* = | 0.2| was chosen, as it yields the largest sample size. Using the UCSF sample size calculator, the sample size needed to detect a correlation as small as | 0.2|, at 80% power and 5% type I error, is determined at 194. For this study, correlations less than 0.20 would be too small to be considered clinically significant (37). Given the high attrition rate seen in previous birth cohorts (37), we estimate that roughly 15% of the participants will drop out after the first visit. An additional 10% was factored into for losses due to preterm delivery or still birth. More participants (∼10% of sample) are also required to test for simple interactions in our study (e.g., Emirati, Sex, and Timing). Thus, the original sample size was increased by 35% and the intended sample size was determined at 260 pregnant women.

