Frequencies and percentages will be used to describe categorical variables and mean, and standard deviations will be used to describe continuous variables. The chi-square test (χ2) or Fisher’ s exact test will be used to calculate the association between categorical variables. Independent *t*-tests and Mann-Whitney tests will be used to chart comparisons for normal and non-normal continuous variables, with normality of variables evaluated using the Kolmogorov-Smirnov and Shapiro-Wilk tests. Associations among the variables of the cohort study (i.e., maternal factors, birth outcomes, breastfeeding, complementary feeding, growth patterns, etc.) will be examined using simple linear and logistic regressions. The two main dependent variables in this study are related to birth outcomes and growth patterns of the child. Variables showing statistical significance in the univariate analysis will be included in the multivariate models as covariate factors in order to control for potentially confounding variables that have been used in the model. Parameter estimates and their respective 95% confidence intervals will be calculated for linear regression analyses, whilst for logistic regression analyses odds ratios and their respective 95% confidence intervals will be calculated. Tests for linearity (tolerance > 0.4) of the covariates included in the regression models will be performed. Normality of the residuals will be assessed using the histogram of standardized residuals and normal probability plot in all linear regression models. *P*-values less than 0.05 will be considered to indicate statistical significance.

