The overall prevalence of global developmental delay and pervasive developmental disorder among 3-year-old children in the UAE in 2016 was reported to be 2.44% and 29/10,000 for severe delay/disorder with a prevalence of 8.4% and 58/10,000 for mild to moderate delay/disorder, respectively, with no reports profiling the neurodevelopment abilities of young children during the first 1,000 days of life from UAE (28). Therefore, the importance of the first few years of a child’s life to decreasing the risk of disease morbidity, mortality, and later risk of chronic disease, and to promoting healthy growth and development, is important. Moreover, nutrition during the first 1,000 days of a child’s life has been identified as one of the significant modifiable factors, during this critical window of opportunity, to influence optimal growth, promote optimal neurodevelopment and reduce disease vulnerability later in life (61). In addition, the data obtained in this study will support the development and validation of a new tool, the Neo-NDA, to be used for the measurement of neurological status and maturity of new-borns in the UAE; explore the association between early childhood development (ECD) outcomes using the three inter-related tools: Neo-NDA, the OX-NDA and the INTER-NDA at < 5, 12, and 24 months of life; and use holistic and standardized measures of ECD, importantly including measure of vision, hearing and sleep at all developmental assessments. Prenatal maternal nutrition is an important predictor of fetal and child brain development, exerting its effect in both intrauterine (fetal growth and birth outcomes) and extrauterine (parenting, child feeding practices, maternal mood, quality, and quantity of breast milk) environments. There is limited understanding on what constitutes optimal ECD, with most studies employing heterogeneous methodologies for ECD assessment and being carried out in high-income western settings. This has limited both the comparability and generalizability of neurodevelopmental evaluations, between studies, and to other populations. It also restricts their scalability for measuring and monitoring ECD at a population level with routine ECD screening programs lacking in many parts of the world. To our knowledge, there are no studies profiling neurodevelopmental outcomes during the first 1,000 days of life in the UAE, and therefore our findings will fill this gap. There is a need for high quality data to be collected in country/geography-specific large birth cohorts, using standardized methodologies, to guide understanding of what constitutes optimal and sub-optimal child development in these contexts, to permit comparability between populations, representing a scalable solution to the application of ECD surveillance in these settings. Birth cohort studies that commence either during pregnancy or preconceptionally and then follow the offspring and the wider family into later life, can make a significant contribution to the development of dietary recommendations to expectant mothers during pregnancy to maximize the health and development of the offspring while simultaneously contributing to the understanding of optimal and sub-optimal ECD outcomes in the context of maternal nutrition. Maternal and infant nutrition, as well as early child growth, health, and development, should be a priority for health policy implementation, health promotion activities, and interventions.

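### Covariates are selected by univariate significance to control confounding; the rule can miss real confounders and does not keep out variables that follow the maternal exposure

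*Protocol article*

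**What the plan says.** All of the analysis text is in the protocol article, Statistical Analysis and Sample Size Calculation.

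- Primary aim: "The primary aim of the study is to examine the associations between maternal nutrition" and infant health outcomes.
- Outcomes: "The two main dependent variables in this study are related to birth outcomes and growth patterns of the child".
- Variables analysed: "Associations among the variables of the cohort study (i.e., maternal factors, birth outcomes, breastfeeding, complementary feeding, growth patterns, etc".) by simple linear and logistic regression.
- Covariate rule: "Variables showing statistical significance in the univariate analysis will be included in the multivariate models as covariate factors".
- Purpose of the rule: "in order to control for potentially confounding variables that have been used in the model".
- Threshold: P below 0.05.

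Two other sections bear on how the analysed variables relate to the exposure. The Discussion describes prenatal maternal nutrition as "exerting its effect in both intrauterine (fetal growth and birth outcomes) and extrauterine (parenting, child feeding practices, maternal mood" and breast milk). The Introduction says its influence continues after birth "by impacting the quality and quantity of breast milk, maternal mood, and infant feeding practices".

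**The concern.** The rule is meant to control confounding, but its criterion measures something else. A univariate p-value reflects the strength of an association and the sample size. It does not show whether a variable is a common cause of exposure and outcome. Two errors can follow.

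1. **Confounders left out.** A confounder of modest strength often fails a 5% test at this sample size. One whose effect runs against the exposure effect can look unrelated to the outcome on its own, and then it is dropped most of the time.
2. **Consequences of the exposure let in.** Birth outcomes and infant feeding are among the variables analysed, and the article itself describes them as routes by which maternal nutrition acts. A good predictor of growth will nearly always be significant. Nothing in the rule stops it from being treated as a confounder in a model of maternal nutrition and postnatal growth, where it would remove part of the effect under study.

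At stake are the adjusted estimates for the primary aim. The adjustment set would also vary from outcome to outcome partly by chance.

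**Working it through.** **1. The plan's own figure.** Inputs from the article: r=0.2, 80% power, 5% type I error. For one correlation by Fisher's z, two-sided:

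n = ((1.960 + 0.842) / atanh(0.2))² + 3 = (2.802 / 0.2027)² + 3 = 193.97, so 194.

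This reproduces the stated 194. Then 194 × 1.35 = 261.9, close to the stated 260. After the stated losses of 15% and 10%, 260 × 0.75 = 195 women remain.

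**2. How often the screen misses a real predictor.** With d = atanh(r) × √(n − 3), the chance of P<0.05 is approximately Φ(d − 1.96). For n=195 and r=0.15, d = 0.1511 × √192 = 2.094, so the variable is kept 55% of the time and missed 45%.

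| True r with outcome | Missed, n=195 | Missed, n=260 (no losses) |
|---|---|---|
| 0.12 | 61% | 51% |
| 0.15 | 45% | 32% |
| 0.20 | 20% | 10% |
| 0.25 | 6% | 2% |

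**3. Residual confounding when there is no true effect.** Simulation with n=195, 4,000 data sets per row, standardised variables and independent confounders. The path strengths are assumptions; the documents give none.

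| Confounders | Path to exposure | Path to outcome | Type I error, screened | Bias (SD) |
|---|---|---|---|---|
| 4 | 0.35 | 0.13 | 16% | 0.08 |
| 4 | 0.20 | 0.13 | 8% | 0.04 |
| 4 | 0.35 | 0.25 | 7% | 0.02 |
| 2 | 0.20 | 0.13 | 5.5% | 0.02 |
| 1 | 0.35 | 0.13 | 5% | 0.015 |

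With all four confounders of the first row fixed in advance, the type I error is 5% and the bias is zero.

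**4. A confounder that masks the effect.** n=194, true effect 0.20, one confounder with path 0.4 to 0.5 to the exposure and −0.08 to −0.20 to the outcome (assumed). The screen keeps it in only 5% to 29% of data sets, and the mean estimate is 0.14 to 0.17. Adjusting for it regardless of its p-value returns 0.20.

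**5. A mediator in the model.** n=194, total effect 0.20, which is the plan's design value. With m the path from exposure to mediator, k the path from mediator to outcome and d the direct effect, total = d + m × k. The paths are assumed.

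| m | k | d | Mediator kept | Mean estimate, screened | Power, mediator left out | Power, screened |
|---|---|---|---|---|---|---|
| 0.20 | 0.40 | 0.12 | 100% | 0.12 | 80% | 44% |
| 0.30 | 0.30 | 0.11 | 99.8% | 0.11 | 80% | 34% |
| 0.25 | 0.40 | 0.10 | 100% | 0.10 | 81% | 32% |
| 0.30 | 0.40 | 0.08 | 100% | 0.08 | 80% | 22% |
| 0.40 | 0.40 | 0.04 | 100% | 0.04 | 81% | 9% |

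The loss of effect runs from (0.20 − 0.12)/0.20 = 40% to (0.20 − 0.04)/0.20 = 80%.

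**The case against.** - **The list is not called a covariate pool.** It names variables whose associations will be examined and includes the outcomes themselves, and the covariate sentence speaks only of potential confounders. A reader might infer that the article plans to adjust for mediators. It does not say so. What stands is narrower: the rule admits whatever is significant, and nothing keeps post-exposure variables out.
- **The rule is not expressly exclusive.** The text says significant variables go in; it does not say that no others may. That is correct, but the article names no other basis for adjustment.
- **Mediation is limited to some models.** It concerns maternal exposures with postnatal outcomes. When a birth outcome is the dependent variable, feeding comes later and is no mediator. For the early-feeding objective, birth size and gestational age precede the exposure and can be proper confounders. The statements in the Introduction and Discussion about routes of action are also made about neurodevelopment; for growth, they apply by extension.
- **The 16% is a severe case.** Four confounders at 0.35 explain 4 × 0.35² = 49% of the exposure variance, act in one direction and are each weak enough to be missed often. Milder settings give 5% to 8%, and strong confounders usually pass the screen.
- **The p-values are not a separate harm.** One might count p-values made too small by screening as a further problem. In these simulations the excess type I error follows the bias and disappears when the bias is small, so the two are largely the same harm.
- **The aim is association.** That is the wording, but the stated reason for adjustment is confounding, and the Objectives speak of effect and impact.

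**Conclusion.** The concern holds within these limits. The covariate rule is stated in the article, so it is not a detail left to an analysis plan, and it does not serve its stated purpose. The miss rates in step 2 depend only on n and r. All other sizes rest on assumed paths and should be read as ranges.

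Over-adjustment is the larger risk for maternal exposures and postnatal growth, because a mediator that predicts growth almost always passes the screen. The article's power figure would not apply to such a model. Residual confounding is likely but not certain, and it is small when confounders are few or strong.

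This should be fixed. It falls short of a must-fix because the bias depends on unknown correlations, the aim is worded as association, and the main candidate confounders are already collected, so nothing is lost for good.

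**What to change.** Replace the screening sentence with an adjustment set fixed in advance for each exposure-outcome pair. Derive it from subject-matter knowledge, for example a causal diagram, and keep it whatever the p-values.

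- **Candidates already collected:** maternal age, education, income and lifestyle (sociodemographic questionnaire), BMI from first-trimester height and weight, infant sex (birth records) and region (recruitment strata).
- **Maternal exposure, postnatal outcome:** leave gestational age at birth, birth size and infant feeding out of the total-effect model. Use them only in models labelled as mediation or direct-effect analyses.
- **Birth outcomes:** do not adjust for later feeding.
- **Early feeding and growth:** birth size and gestational age precede the exposure and may be kept as confounders.

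The change should be made before outcome data are examined. It costs wording and a few degrees of freedom per model; no new data are needed, and 194 and 260 stay as they are.

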Maternal and infant nutrition may influence the risk of later disease due to its critical associations with immunological development of the fetus and young infant (23). Adequate nutrition is necessary both for establishment of the immune system, normal organogenesis and development, and development of an adequate immune response. Undernutrition during early childhood exerts a concomitant effect on cognitive and developmental milestones through mid- and late- childhood and into adolescence. Studies consistently identify associations between stunting at ages 2 and 3 years with later cognitive deficit, as well as school achievement, even after controlling for socio-demographic confounders (24).

Global estimates of stunting and wasting in children under the age of five for 2018 were reported to be 21.9% (149 million) and 7.3% (49 million), respectively, and obesity in children of the same age group was reported to be 5.9% (40 million). The MENA region has the second highest rate of under 5 years overweight children, with an increase from 8.9% in 2,000 to 11.2% in 2018 (25). According to the UNICEF, in 2020 the UAE mortality rate for children under five was 6.6 per 1,000 live births, for infants was 5.6 per 1,000 live births, and neonatal mortality rate was 3.6 per 1,000 births (26). The percentage of overweight school and adolescent children (5–9 years) was estimated to be 37% in 2016 (27). However, there are no records for malnutrition, stunting and wasting of children in the country.

In some research from the UAE, the overall prevalence of global development delay and pervasive development disorder among 3-year old children was reported to be 2.44% and 29 in 10,000 for severe development delay/disorder with a prevalence of 8.4% and 58 in 10,000 for mild to moderate delay/disorder (28). Currently, there are no reports of the neurodevelopmental abilities of young children during the first 1,000 days of life from the UAE. These indicators are considered key public health factors, which contribute independently to mortality and burden of disease.

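### Logistic models for binary birth outcomes set no limit on covariates; at about 19–26 events (assuming a 10% rate), 9–10 covariates inflate the log odds ratio by roughly 5–17%, which a penalised fit and a short fixed list would largely avoid

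*Protocol article*

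**What the plan says.** All of this is in the protocol article, section Statistical Analysis and Sample Size Calculation, unless stated.

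- Associations are to be examined by linear and logistic regression. Birth outcomes and child growth are the two main dependent variables. For the logistic models, "whilst for logistic regression analyses odds ratios and their respective 95% confidence intervals will be calculated".
- Any variable significant in univariate analysis goes into the multivariable model as a covariate. No maximum number of terms, check of events per variable, or penalised or exact regression method is stated. The one check on covariates, tolerance above 0.4, measures collinearity, not the number of terms.
- The sample size rests on a correlation: "the sample size needed to detect a correlation as small as" 0.2, "at 80% power and 5% type I error, is determined at 194". Then "the original sample size was increased by 35" per cent and "the intended sample size was determined at 260 pregnant women". No binary outcome was sized.
- Two loss allowances enter that increase: "we estimate that roughly 15% of the participants will drop out after the first visit", and "An additional 10% was factored into for losses due to preterm delivery or still birth".
- The Objectives list preterm birth and small- and large-for-gestational-age birth weight among the factors studied. They also list eight maternal blood markers and gestational weight gain as exposures, with social, dietary, activity and stress factors besides.

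**The concern.** A logistic model draws its information mainly from the rarer outcome class. If a binary birth outcome occurs in about a tenth of women, a cohort of this size has only about two dozen events. The entry rule could still bring in many terms from a large candidate pool. With few events per variable, maximum likelihood pushes odds ratios away from 1 and makes them less precise.

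This is separate from the choice of confounders: a well-chosen list of nine or ten would still be long for so few events. At stake is the reliability of adjusted odds ratios for outcomes such as preterm birth or small-for-gestational-age birth, in a study that says it will inform policy.

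**Working it through.** **1. The plan's own figure.** Inputs: r = 0.2, 80% power, 5% two-sided error. n = ((1.960 + 0.842)/atanh 0.2)² + 3 = (2.802/0.2027)² + 3 = 193.97, so 194, as stated. Then 194 × 1.35 = 261.9, given as 260. Both reproduce. No event rate or odds ratio enters.

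**2. Events.** Analysable women: between 194 (the base size) and 260 (all recruited); after the 15% and 10% losses, 260 × 0.75 = 195. The outcome rate is an assumption, 10%. The only nearby figure is the combined preterm or stillbirth loss allowance, which is not given as an outcome rate.

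- At 10%: 194 × 0.10 = 19.4 to 260 × 0.10 = 26.0 events.
- At half that rate: 9.7 to 13.0. At one and a half times: 29.1 to 39.0.

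**3. Events per variable.** Eight blood markers plus weight gain make nine candidates before any social or lifestyle factor: 19.4/9 = 2.2 to 26.0/9 = 2.9. With ten terms: 1.9 to 2.6. A rule of thumb of ten events per term (not in the article) would allow one or two terms.

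**4. Bias of ordinary maximum likelihood.** Simulation, 600 cohorts per cell, 10% events. Assumed: independent covariates, odds ratio 1.5 per SD for continuous ones, odds ratio 2 for binary ones with 20% prevalence. Change in log odds ratio for the continuous covariates:

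| Covariates | n = 195 | n = 260 | Failed fits | 95% CI coverage |
|---|---|---|---|---|
| 1 | +2% | −1% | 0% | 95–96% |
| 3 | +9% | +3% | 0–0.3% | 94–96% |
| 6 | +6% | +7% | 0–0.8% | 95% |
| 10 | +17% | +11% | 0–0.7% | 95% |

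Monte Carlo error for a single coefficient is about 1/√(195 × 0.10 × 0.90) = 0.239, divided by √600 and by ln 1.5 = 0.405. That is 2.4 percentage points, and less where several coefficients are averaged. The +9% beside +6% in the first column is therefore partly noise.

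On the odds-ratio scale, a true 1.5 becomes 1.5^1.05 = 1.53 at 5% inflation and 1.5^1.17 = 1.61 at 17%.

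A second set, 1,000 cohorts per cell with covariates correlated 0.3, gave 0–5% bias with five or fewer covariates and at least 20 events. With eight or ten covariates it gave +11% and +14% at n = 260, and +15% and +26% at n = 195. The 26% is the most adverse cell.

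**5. Against Firth's method.** With nine fixed covariates at 10% events and n = 195 to 260, maximum likelihood inflated the log odds ratio by 5–15%. Firth's estimate was off by about −3% to +2%, and its root mean squared error was about 5–14% lower in every cell.

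**6. How many variables would enter.** Simulating the screen with 15 candidates, three of them with a true odds ratio of 1.5, a median of 2 to 7 entered and no fit failed. Under other assumptions on the number of candidates and their correlation, the median ran from 1 to 18. The article does not settle this number.

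**The case against.** Five arguments weigh against the point.

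- **The 10% is a loss allowance.** It combines preterm delivery with stillbirth and puts no ceiling on events. This stands, so the 19–26 events are an assumption, not a figure the protocol sets.
- **No binary birth outcome is named for a logistic model.** The wording of the Objectives even places preterm and small- or large-for-gestational-age birth among the antenatal factors. This stands in part. Logistic regression is planned and birth outcomes are a main dependent variable, so such models are the natural reading, but the examples are inferred.
- **Model size is unknown and the harm moderate.** This also stands: few variables may pass the screen, and coverage stayed at 94–96%.
- **Continuous outcomes already carry much of the study.** The sizing rests on a correlation, linear regression is planned, and gestational age and birthweight are collected. True, but the article does not say that they take precedence over the binary forms.
- **A full analysis plan could handle sparse data.** The absence of Firth's method from an article would be no fault by itself. The entry rule, however, is stated here and has no limit, and that is what needs changing.

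A stronger reading is tempting. The Introduction cites developmental delay and disorder rates of "2.44% and 29 in 10,000 for severe development delay/disorder with a prevalence of 8.4% and 58 in 10,000 for mild to moderate delay/disorder", and 0.0244 × 195 = 4.8 might suggest models with five events that cannot be fitted. The article does not support this. Those are background rates in 3-year-olds, whereas follow-up ends at 22–26 months. The development tools are scored on five-point scales, and nowhere is delay made a logistic outcome.

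**Conclusion.** The point holds in a limited form. The stated rule lets any number of terms into ordinary logistic models for binary birth outcomes, and at about 19–26 events only a few covariates can be supported. With nine or ten, the log odds ratio is inflated by roughly 5–17%, more in one adverse correlated setting, and is less precise than a penalised estimate. With five or fewer the bias is small. Fits rarely fail at these event counts.

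The size rests on an assumed 10% outcome rate, true odds ratios near 1.5 per SD, and a model that reaches nine or ten terms. None of these is in the article. A reader might infer that the published odds ratios will necessarily be inflated; that does not follow, because it depends on how many variables enter. This is a modest weakness with a nearly free remedy.

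Separately, two places need reconciling. The sample-size paragraph counts preterm delivery as a loss, while the Objectives list preterm birth among the factors studied. If preterm births leave the analysis, a preterm model has no events at all.

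**What to change.** In Statistical Analysis and Sample Size Calculation:

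1. For binary birth outcomes, use Firth penalised logistic regression with profile-likelihood confidence intervals.
2. Replace entry by univariate significance with a short covariate list fixed in advance, its length set by the expected number of events for each outcome. State the assumed rate.
3. Make the continuous form already collected (gestational age, birthweight) the main analysis, with the binary form secondary.
4. State whether preterm births are analysed or treated as losses, and make the sample-size paragraph and the Objectives agree.

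The cost is wording, a penalised-likelihood routine in the software, and fewer covariates in the binary models, so adjustment there is less complete. No change to recruitment or data collection is needed.

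### The stated test for linearity, tolerance above 0.4, measures collinearity and cannot detect a non-linear covariate-outcome relation

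*Protocol article*

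**What the plan says.** All the relevant text is in the protocol article, Statistical Analysis and Sample Size Calculation.

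- Models: associations among maternal factors, birth outcomes, feeding and growth "will be examined using simple linear and logistic regressions", followed by multivariable models.
- Covariate entry: "Variables showing statistical significance in the univariate analysis will be included in the multivariate models as covariate factors".
- Linearity: "Tests for linearity (tolerance > 0.4) of the covariates included in the regression models will be performed".
- The only other model check: "Normality of the residuals will be assessed using the histogram of standardized residuals and normal probability plot in all linear regression models".

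The article does not use the word collinearity. It names no residual-versus-predictor plot, polynomial or spline term, or check of linearity in the logit. It does not say what happens to a covariate whose tolerance is 0.4 or lower.

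**The concern.** The sentence gives a purpose, testing linearity, and a criterion, tolerance, that cannot serve it. Tolerance is calculated from the covariates alone, so it is the same whether the outcome rises in a straight line, levels off or turns back. An analyst who follows the sentence literally would report linearity as verified when it had not been examined.

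This bears on the primary aim, which relates maternal weight gain and micronutrient status to infant outcomes through linear and logistic regression. The Introduction describes micronutrient effects largely in terms of deficiency, and that leaves room for a threshold. If a relation bends, a straight-line term gives a distorted or weakened estimate, and the stated check would not show it. A weakened linear term may also fail the univariate significance screen, so the variable would not reach the multivariable model.

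**Working it through.** **1. The plan's own figure.** The section says "the sample size needed to detect a correlation as small as | 0.2" in absolute value "at 80% power and 5% type I error, is determined at 194". By Fisher's z, two-sided (sidedness is not stated, so this is assumed):

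n = ((1.960 + 0.842) / atanh(0.2))² + 3 = (2.802 / 0.2027)² + 3 = 193.97, which rounds up to 194.

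This reproduces. With the 35% increase, 194 × 1.35 = 261.9, close to the stated 260. The point does not depend on these figures; 194 only sets the size of the simulations.

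**2. What the criterion measures.** For covariate j, tolerance = 1 − R²ⱼ, where R²ⱼ comes from regressing covariate j on the other covariates.

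- Tolerance > 0.4 is the same as R²ⱼ < 0.6.
- VIF = 1 / tolerance, so the cut-off is 1 / 0.4 = 2.5.
- With two covariates it means |r| < √0.6 = 0.775 between them.
- With a single predictor there is nothing to regress on, so R²ⱼ = 0 and tolerance = 1. In the simple regressions the rule passes by definition.

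**3. Does it respond to non-linearity?** Simulation with n = 194, 2,000 replicates, standard normal x, unit-variance noise and one independent covariate. The truth is assumed to be y = 0.3x² + noise.

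| Quantity | Result |
|---|---|
| Tolerance > 0.4 | 100% of runs (minimum 0.93) |
| Linear term significant | 12% |
| Quadratic term significant | 99.9% |

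The rule passes a clearly curved relation every time.

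**4. Does it pass a truly linear relation?** The truth is y = 0.3x + noise, with a second covariate correlated 0.9 with x. Mean tolerance was 0.19 and the rule failed in 100% of runs. A quadratic term was significant in 4%, about the nominal 5%. So the rule tracks correlation among covariates and not the shape of the relation to the outcome.

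**5. Would the residual plots catch it?** The Shapiro-Wilk test on residuals from the straight-line fit stands in for the histogram and probability plot (n = 194, 2,000 replicates).

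| Assumed truth | Normality rejected |
|---|---|
| y = x² + noise | about 99% (mean residual skewness about 1.3) |
| y = 0.3x² + noise | about 13 to 14% |

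A strong curve would show up in the residual plots, although they would not identify curvature as the cause. A moderate one usually would not. For logistic models no such plot is planned.

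**6. Scale of the assumed curve.** Var(0.3x²) = 0.09 × 2 = 0.18, which is 0.18 / 1.18 = 15% of the outcome variance. A correlation of 0.2 explains 0.2² = 4%. The example is therefore a larger effect than the smallest one the study is sized for, and the residual plots still miss it in most runs.

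**The case against.** The best defence is that one word is wrong. A tolerance cut-off applied to the covariates in a model is a routine collinearity check, and linearity was probably written for collinearity. Read that way the procedure is valid, and the lack of a functional-form check is the kind of detail that a condensed article may leave to a fuller plan. The slip is plausible, and a fuller plan that is not shown may hold a real check. But the sentence still needs correcting on this reading, because it assigns a named diagnostic to the wrong assumption. Once it is corrected, no linearity check remains in the published text.

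Three stronger conclusions are tempting and are not supported:

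- **That a non-linear association would be missed entirely.** A symmetric U centred on the exposure mean is a worst case. In the strong version the planned residual plots would very likely raise a flag, and milder or asymmetric curvature would distort an association rather than hide it.
- **That the 0.4 cut-off would remove genuine confounders.** The text says only that tests will be performed and states no removal rule.
- **That these exposures are known to act in a U-shape.** The article does not say so. For weight gain the Introduction describes a one-directional relation, with low gain linked to low birth weight and excess gain to high birth weight. Deficiency effects of micronutrients are also one-directional, though a threshold is possible.

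**Conclusion.** The point holds as an error of statement. The criterion given for linearity is a collinearity criterion (VIF below 2.5) and cannot detect non-linearity. This follows from the definition and needs no assumption. The simulated rates do rest on assumptions: normal covariates, unit-variance noise, the chosen curves and n = 194. They show that the one remaining check is a weak safeguard against moderate curvature in linear models (about 13 to 14% flagged, against 99.9% for a quadratic term), and that logistic models have none.

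The conclusion applies to the plan as published. It does not show that any particular exposure is non-linear. It changes no sample size, type I error rate or stated estimate. It should be corrected because it touches the primary-aim models and is cheap to put right, but it is not a flaw in the design.

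**What to change.** 1. Relabel the tolerance rule as a collinearity diagnostic.
2. For the main continuous maternal exposures (gestational weight gain and the micronutrient biomarkers), state in advance one functional-form check: a quadratic or restricted cubic spline term tested against the linear term, with residual-versus-predictor plots. Say beforehand how the result will be used, so that the model is not chosen after seeing the data.
3. For logistic models, state a check of linearity in the logit.

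Cost: a sentence or two of text, 1 to 2 degrees of freedom per exposure, and a little more routine analysis. No change to sample size, alpha or data collection.
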